## Abbreviations

|        |   |                                                    |
|--------|---|----------------------------------------------------|
| AFT    | - | Affordable Fluoride Toothpaste                     |
| ART    | - | Atraumatic Restorative Treatment                   |
| BPOC   | - | Basic Package of Oral Care                         |
| CAST   | - | Caries Assessment Spectrum and Treatment           |
| DMFT   | - | Decayed Missing Filled Teeth                       |
| DEBS   | - | District Education Board Secretaries               |
| ICC    | - | Intra-Cluster Correlation Coefficient              |
| LMICs  | - | Low and middle-income countries                    |
| MUHAS  | - | Muhimbili University of Health and Allied Sciences |
| NCDs   | - | Non-Communicable Diseases                          |
| OHE    | - | Oral Health Education                              |
| OHRQoL | - | Oral Health Related Quality of Life                |
| OIDP   | - | Oral Impacts on Daily performance                  |
| OUT    | - | Oral Urgent Treatment                              |
| SB-FMR | - | School Based Fluoride Mouth Rinse                  |
| SES    | - | Socioeconomic status                               |
| SSA    | - | Sub Saharan Africa                                 |
| STB    | - | Supervised Tooth Brushing                          |
| TDRC   | - | Tropical Diseases Research Control Institute       |
| WHO    | - | World Health Organization                          |

## **Definition of key terms**

### **Adolescent**

World Health Organization (WHO) defines an adolescent as any person between ages 10 and 19, although other sources incorporate a span of 9 to 26 years (Curtis, A.C., 2015). WHO definition will be adopted in this study.

### **Basic Package of Oral Care (BPOC):**

Is an intervention comprising of oral urgent treatment (OUT); atraumatic restorative treatment (ART) and affordable fluoride toothpaste (AFT) designed by WHO to improve oral health in low and middle-income countries (Batra *et al.*, 2014).

### **Dental caries**

Is a biofilm-mediated, dynamic multi-factorial disease that results in the phasic demineralization and remineralization of dental hard tissues (Pitts *et al.*, 2017). In this study diagnosis of dental caries will include any visible change of enamel color or **translucency** to extensive distinct cavity with visible dentin or pulp exposure.

### **Dental plaque**

Is a sticky colorless or pale yellow to brown biofilm or mass of bacteria that grows on tooth surface (Murakami *et al.*, 2018).

### **Gingivitis**

Is a site-specific inflammatory condition initiated by dental biofilm accumulation and characterized by gingival redness and edema and the absence of periodontal attachment loss (Trombelli *et al.*, 2018).

### **Oral health**

Is the ability to speak, smile, taste, chew, swallow and convey a range of emotions through facial expressions with confidence and without pain, discomfort and disease of the craniofacial complex (Lee *et al.*, 2017).

### **Oral health related quality of life**

Is defined as a multidimensional construct that reflects (among other things) people's comfort when eating, sleeping and engaging in social interaction; their self esteem; and their satisfaction with respect to their oral health (Baiju *et al.*, 2017).

**Phase III trials**

**Research** which aims to provide a definitive assessment of the effectiveness of the intervention against the primary outcome(s) of interest (Smith et al., 2015).

**Socio-demographic inequalities in health**

Is any measurable aspect of health that varies across individuals or according to socially relevant groupings such as place of residence, race/ethnicity, occupation, gender, religion, education, socioeconomic status (SES), and social capital or resources (Arcaya et al., 2015).

**Standard of self-care**

encompass oral health care which a participant used to perform before enrollment or will perform during the study such as brushing of teeth, use of fluoridated tooth paste or attending for dental checkup or treatment” without being influenced or monitored by the study administrators.

## Summary

**Background:** Global trends of diseases show an increase of oral diseases in most low and middle- income countries due to increased availability of sugars, inadequate fluoride products and lack of sustainable preventive strategies. Most oral diseases are behavioral related and behaviors acquired during adolescence are likely to be passed to adulthood. Adolescent's oral health behaviors are shaped by family socioeconomic status and therefore socio gradient in oral diseases may be more reflected in this group. Despite increasing oral diseases and World Health Organization (WHO) recommendations of using BPOC as feasible and cost-effective preventive and curative approach of oral diseases, the strategy has not been implemented in Sub-Saharan Africa region.

**Aim:** To evaluate the effectiveness of applying the modified WHO basic package of oral care (BPOC) in improving oral health-knowledge and behaviors, oral health and related quality of life among adolescents in Copperbelt, Zambia.

**Materials and methods:** A cluster randomized controlled field trial with a total sample size of 1760 grade eight secondary school adolescents will be done in Copperbelt province, Zambia. Adolescents in the trial arm will receive a modified WHO-BPOC and the control will maintain their standard of care, both groups will be re-assessed at follow-ups. Data collection on adolescents' demographics, oral health-related knowledge and behavior, impacts of oral disease on daily performance and parental socio-demographics will be done using a self-administered structured questionnaire. Data on dentition status, plaque, and gingival bleeding will be assessed using CAST, Silness, and Loe (1967) plaque and gingival bleeding indices, respectively. Data entry, cleaning, and analysis will be done using IBM SPSS for windows (version 23), and summarized as frequency distribution and cross-tabulations. Adjusted binary logistic regression and generalized estimating equation will be performed to examine the differences between the groups at baseline and follow up in oral health-related behaviors, plaque, gingival bleeding, OHRQoL and dental caries status for various socio-demographics characteristics. The statistical significance difference shall be assumed when  $p \leq 0.05$ .

**Budget of the study:** A total budget of TSh 34,341,450.00 is required to facilitate proposal writing, ethical clearance, purchase of dental materials and supplies, thesis writing and other logistics.

## **1.0 Introduction**

### **1.1 Background**

Oral health is an essential part of general health and wellbeing of individuals and societies as it affects general health and quality of life (Lee *et al.*, 2017). Adolescents' oral health depends on oral health-related behaviors (OHRB) such as frequency of tooth brushing, use of fluoridated toothpaste, regular preventive dental checkups, and frequency of consumption of sugary snacks and drinks. Oral health-related behaviors acquired during adolescence are likely to be passed on to adulthood and affect adulthood oral health signifying the importance of this age group (McDade *et al.*, 2011). Socio-economic status of the family influences OHRB as it affects recognition of the importance of oral health, access and affordability to oral health care products such as toothbrushes and fluoridated toothpastes and determines access to preventive and curative services (Jepsen *et al.*, 2017).

Socio-demographic gradient in health is any measurable aspect of oral health that varies across individuals or according to socially relevant groupings such as place of residence, race/ethnicity, occupation, gender, religion, education, socioeconomic status (SES), and social capital or resources (Arcaya *et al.*, 2015). With respect to oral health, oral diseases disproportionately affect the poor and socially-disadvantaged members of societies, even in countries with the most established and universal welfare policies (Bergqvist *et al.*, 2013). Socio-economically deprived individuals tend to have worse clinical oral health and lower Oral Health Related Quality of Life (OHRQoL).

Dental caries and gingivitis are the most common behavioral related oral diseases which affect 40 to 90% of adolescents in LMICs (Benzian *et al.*, 2017). The mean DMFT among 12 years adolescents in African countries currently ranges from 0.3 to 4.9 whereas more than 90% of caries remain untreated (Abid *et al.*, 2015). Severe periodontal problems are uncommon among adolescents, however, gingivitis a mild form of periodontal diseases affects more than 50% of the adolescents before puberty (Abid *et al.*, 2018). In Sub-Saharan Africa, a higher prevalence of dental caries is reported more among girls than boys, individuals of higher than low socioeconomic background and urban than rural residents (Okullo *et al.*, 2004; Artemisa *et*

*al.*, 2010; Mashoto *et al.*, 2010). Poor oral hygiene and periodontal conditions are more reported among boys than girls, individuals with lower than higher socioeconomic status, those living in rural than urban areas and older than younger adolescents (Varenne *et al.*, 2006, Kolawole *et al.*, 2011).

Oral Health Related Quality of Life (OHRQoL) is a concept that reflects people's comfort when eating, sleeping and engaging in social interaction; their self esteem; and their satisfaction with respect to oral health (Baiju *et al.*, 2017). Oral diseases negatively impact on the oral health-related quality of life of children and adolescents (Leal *et al.*, 2012; Peres *et al.*, 2013). Poor oral health during adolescence affects adolescent's food intake, self-esteem, disturb sleep, due to pain and interfere with participation in school activities leading to poor school performance (Ribeiro *et al.*, 2018). Impacts such as pain and perception of appearance are more severe in adolescents than adults as they not only affect their quality of life but also psychological development and social interactions (Peres *et al.*, 2013). A Systematic review of factors influencing oral health-related quality of life in children and adolescents in Africa report Child –OIDP as the most commonly used and validated measure of OHRQoL (Malele-Kolisa *et al.*, 2019). Recent studies in Sub- Saharan Africa (SSA) which used Child-OIDP reported poor oral health- related quality of life in terms of oral impact on daily performance ranging from 35.6 to 54.6% among adolescents. Economically disadvantaged adolescents report significantly poorer quality of life than the socioeconomically advantaged (Mashoto *et al.*, 2010; [name], *et al.*, 2010; Nurelhuda *et al.*, 2010).

Basic Package of Oral Health Care (BPOC) is an intervention recommended by the World Health Organization (WHO) as an affordable and effective preventive and curative modality of oral diseases in developing countries (Batra *et al.*, 2014). The intervention comprises of three components; Oral Urgent Treatment (OUT), Atraumatic Restorative Treatment (ART) and Affordable Fluoride Toothpastes (AFT). Safety and how well the components of the intervention works have been proved in previous studies (Kikwilu *et al.*, 2009; Mashoto *et al.*, 2010), however effectiveness and implementation of the strategy as a package has not been tested in most African countries including Zambia. Modification of the conventional BPOC in this study entail inclusion of oral health education and provision of fluoridated tooth pastes to

encourage use of the oral care products in future. The conventional BPOC make fluoride tooth pastes available and affordable through regulating policies such as reduction or eliminating tax to the products aiming at reducing their market price. This is a level three trial that aims at assessing the effectiveness of the modified BPOC in improving oral health-related behaviors, oral health and related quality of life.

## **1.2. Problem statement**

Dental caries and periodontal diseases affect 40 to 90% of adolescents in LMICs. Most of these diseases remain untreated, thus impacting negatively the adolescents' general health, well-being and quality of life, school performance, and social interactions. Furthermore, in SSA region the diseases accumulate in socio-demographically disadvantaged adolescents in situations where the available oral health systems and services are inadequate to cater for preventive and curative care. The cost of treating dental caries with the curative approach alone exceeds fiscal capabilities of most LMICs including Zambia. Despite evidence of increasing oral diseases and WHO recommendations of using BPOC as a cost-effective oral disease preventive and curative approach the strategy has not been tested and implemented in the Sub-Saharan Africa region, Zambia inclusive. Therefore, this study aims at assessing the effectiveness of the modified BPOC in improving oral health knowledge and related behaviors, oral health and related quality of life among Zambian Adolescents.

### 1.3. Conceptual framework

[figure not shown]

**Figure 1 Conceptual framework Modified from 2002 WHO Risk factor model for promotion of oral health (Petersen, P.E., 2005)**

Adolescent's demographics (age and sex) and parental/guardians (education and SES) affect oral health related-behaviors and oral health. Application of a 6 months modified BPOC will lead to an improvement in oral health-related behaviors such as brushing teeth two times a day, use of fluoridated tooth paste, reduced risky sugar consumption and dental checkups at least once a year. Improved health-related behaviors will ultimately lead to improvement in adolescent's oral hygiene and health status. Improvement in adolescent's oral hygiene and health status ultimately lead to reduced impacts in oral health-related quality of life among adolescents. The intervention can also directly improve adolescent's oral hygiene and health status and reduce impacts on adolescents OHRQoL.

#### ***1.4. Rationale***

Oral health services in Zambia have been inclined towards curative rather than preventive approach for a number of decades due to lack of emphasis, planning, budgeting and funding of preventive services. The curative approach relies on inadequate number and un evenly distributed dental clinics which are mainly concentrated in urban areas. Most of the clinics render limited services mainly extraction of teeth, due to lack of enough funds to procure equipment and materials for restorative services. Accessibility and affordability of available curative services is a challenge especially among rural communities which may potentially create oral health inequalities. World Health Organization (WHO) recommended Basic Package of Oral Care (BPOC) as an easy to conduct, cheap, and effective strategy in prevention and management of oral diseases in low to middle income countries. Despite of potential benefits the strategy has not been tested and used in most countries including Zambia. The shortfall could be explained by inadequate advocacy of importance of preventive over curative oral health services during training and oral health services delivery, inadequate planning and budgeting for oral health research and preventive services, and lack of oral health data compared to other NCDs in some African countries including Zambia. One of the targets of 2017-2021 Zambia National Health strategic plan is to strengthen and orient health systems to address the prevention and control of NCDs and the underlying social determinants through people-centered primary health care and Universal Health Coverage. This goal

cannot be realized without evidence-based results of the magnitude of non-communicable disease in particular oral diseases and effectiveness of preventive strategies such as WHO-BPOC. This study will highlight the magnitude of dental caries and gingivitis among adolescents and effectiveness of WHO-BPOC strategy in oral diseases prevention. The data will help oral health planners to convince policy makers and planners at ministry of health to plan for preventive oral health services in the country. The study will also improve training of the fifty-year bachelor of dental surgery students who will be involved during execution of BPOC components (OUT, AFT and ART) under supervision. The training will not only impart knowledge on prevention to the dental students but also orient them towards diseases prevention. The study will also contribute towards realizing the 2017-2021 strategic plan goal of creating sustainable and peoples – centered primary health care by empowering students and teachers assigned to the project with knowledge to give oral health education.

## **1.5. Research hypothesis and Questions**

### **1.5.1 Hypothesis**

#### **Null hypothesis**

Curative and preventive measures given through a modified WHO -BPOC has no effect on oral health knowledge and related behaviors, quality of life and socio-demographic gradient in oral health of adolescents in Copperbelt province, Zambia.

#### **Alternative hypothesis**

Curative and preventive measures given through a modified WHO -BPOC has effect on oral health knowledge and related behaviors, quality of life and socio-demographic gradient in oral health of adolescents in Copperbelt province, Zambia.

### **1.5.2 Research questions**

1. What is the extent of poor oral hygiene, gingivitis, dental caries, and OHRQL among adolescents in Copperbelt province, Zambia?
2. What are the determinants of poor oral hygiene, oral health and OHRQoL among adolescents in Copperbelt province, Zambia?
3. Does modified –WHO Basic Package of Oral Health Care (BPOC) have effect on improving oral health, related behaviors and OHRQoL among adolescents in Copperbelt province, Zambia?
4. Does modified –WHO Basic Package of Oral Health Care (BPOC) have effect on reducing socio-demographic gradient in oral health, related behaviors and OHRQoL among adolescents in Copperbelt province, Zambia?

## **2.0. Objectives**

### **2.1. Broad Objective**

To evaluate the effectiveness of applying the modified WHO basic package of oral care (BPOC) in improving oral health knowledge and related behaviors, oral health and OHRQoL among adolescents in Copperbelt, Zambia

### **2.2. Specific Objectives**

- 1 To determine prevalence and distribution of dental caries, periodontal conditions and oral impacts on daily performance among adolescents in Copperbelt Province, Zambia
- 2 To determine the association between dental caries and oral health related quality of life among adolescents in Copperbelt Province
- 3 To assess the effects of a six months modified basic package of oral care intervention on knowledge and behaviors related to dental caries after 18 and 24 months of follow up.
- 4 To assess the effects of a six months modified basic package of oral care intervention on prevalence of dental caries after 18 and 24 months of follow up
- 5 To assess the effects of a six months modified basic package of oral care intervention on prevalence of oral impacts on daily performance after 18 and 24 months of follow up

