#### **4.6. The trial intervention**

The trial intervention is a modified WHO –BPOC which include all the 3 packages of BPOC plus oral health education. The first package, Oral Urgent Treatment (OUT) will include simple extraction of teeth beyond restorable condition and referral for teeth requiring clinic set up for removal. The second package which is Atraumatic Restorative Treatment (ART) will be executed using hand instruments only by removing decayed part of teeth with cavities not reaching the pulp or not diagnosed as irreversible pulpitis then filling with Fuji IX Glass- ionomer. The third component (Affordable Fluoridated Tooth pastes) will be done by providing 250g pack of fluoride toothpaste every two months and toothbrushes every three months for 18 months. In addition to WHO-BPOC the study will also give peer provided oral health education. The peer educators will be furnished with the following printed messages to deliver to their classmates in the intervention groups once after every two weeks for a period of 18 months;

1. Restrict the frequency of taking sugary food and drinks in the diet to less than five times per day.
2. Brush your teeth for 2 minutes ensuring all the surfaces are cleaned; twice per day in the morning and evening before retiring to bed.
3. Use fluoride toothpaste to brush, spit the foam but do not rinse it out.
4. Change your toothbrush every 3 months or when bristles flare out.
5. Advise your parent or guardian to buy a tooth paste containing at least 1450 ppm fluoride and to take you for dental check up at least once a year.

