**Table 1 Summary of intervention set up**

| Baseline
data
collection                                                                                                            | Randomization | Activities in each group                       | Activity Schedule                                |                 |                 |                 |                 |                 |                 |                 |                 |         |                  |
|-------------------------------------------------------------------------------------------------------------------------------------------|---------------|------------------------------------------------|--------------------------------------------------|-----------------|-----------------|-----------------|-----------------|-----------------|-----------------|-----------------|-----------------|---------|------------------|
|                                                                                                                                           |               |                                                | Months                                           |                 |                 |                 |                 |                 |                 |                 |                 |         |                  |
|                                                                                                                                           |               |                                                | 1-2                                              | 3-4             | 5-6             | 7-8             | 9-10            | 11-12           | 13-14           | 15-16           | 17-18           | 19-24   |                  |
| 

• OHK

• OHRB

• Plaque

• Gingival bleeding

• Dental caries

 | Intervention  | 1. Peer led OHE                                | OHE once after every 2 weeks (total 36 sessions) |                 |                 |                 |                 |                 |                 |                 |                 | -No OHE |                  |

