#### **4.6.2. Intervention period**

The intervention will be instituted immediately after base line data collection and randomization and will be for a period of 24 months follow up.

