##### **Mitigation**

- 1 Dental caries assessment using CAST (Frencken *et al.*, 2011) will be used to capture incremental stages of dental caries development and dental caries variable will continue being followed up after 24 months.
- 2 The data analyst will be blinded during analysis stage to avoid subjective decisions on handling missing data, transforming variables, undertaking subgroup analysis, and selecting covariates due to prior knowledge of treatment allocation.
- 3 The interventions will end six months before the last follow up and therefore the effect of adolescents acting due to the reason that their being followed-up will be controlled in the data collected at the last follow up visit.

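### The objectives, conceptual framework and Appendix 6 test a six-month intervention, but section 4.6, Table 1 and section 4.14 run it to month 18, so the 18- and 24-month results have two different meanings

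*Protocol*

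**What the plan says.** **Six months.** Section 2.2, objective 4, is to assess "the effects of a six months modified basic package of oral care intervention on prevalence of dental caries" after 18 and 24 months. Objectives 3 (knowledge and behaviours) and 5 (oral impacts) use the same six-month label and the same visits. Section 1.3 states: "Application of a 6 months modified BPOC will lead to an improvement in oral health-related behaviors". The rows for objectives 3, 4 and 5 in Appendix 6 repeat six months. That makes seven statements in three places.

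**Eighteen months.** Section 4.6 delivers the toothpaste component by "providing 250g pack of fluoride toothpaste every two months and toothbrushes every three months for 18 months", and peer education "once after every two weeks for a period of 18 months". The education row of Table 1, spread over months 1 to 18, begins "OHE once after every 2 weeks (total 36 sessions". The table also places nine toothpaste rounds at two-month steps, and the third urgent-treatment (OUT) and restorative (ART) sessions in months 17-18. All four components are marked as not given in months 19-24. Mitigation 3 in section 4.14 relies on this: "The interventions will end six months before the last follow up".

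**Unclear.** Section 4.6.2, headed as the intervention period, says the intervention "will be for a period of 24 months follow up".

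**Assessment times.** Section 4.9.1 sets follow-up at 6, 12, 18 and 24 months. Section 2.2 assesses objective 4 at 18 and 24 months; the Appendix 6 row for the same objective says 6 and 12.

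**The concern.** The effect objectives say what the trial is to estimate, and here they name a different intervention from the one scheduled. If the package lasts six months, the 18- and 24-month comparisons measure how well an effect persists a year or more after delivery stops. If it lasts 18 months, the first is an end-of-intervention result and the second a short post-intervention result. These support different conclusions from the same data.

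Two of the three objectives concern primary outcomes: section 4.10 lists dental caries status and oral health related quality of life among them. Section 1.4 says the data are meant to help planners make the case for preventive services, so the length and intensity behind any effect are part of the message. Mitigation 3, which controls for behaviour changing under observation, also rests on a stop six months before the last visit. That timing does not hold for a six-month package.

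**Working it through.** **Inputs.** Duration: 6 months (1.3, 2.2, Appendix 6) or 18 months (4.6, Table 1, 4.14). Visits: 18 and 24 months (2.2), or 6 and 12 months (Appendix 6, objective 4). Delivery intervals: toothpaste every 2 months, toothbrushes every 3 months, education every 2 weeks (4.6). OUT and ART sessions: months 1-2, 11-12 and 17-18 (Table 1).

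**1. Which duration produces Table 1's own counts?**
- Toothpaste: 18 / 2 = 9 rounds, as in the table. Six months gives 6 / 2 = 3.
- Education: 36 sessions over 18 months is 2 per month, which reproduces the table's total. At that rate six months gives 12. Counting strict fortnights (30.4375 / 14 per month) gives about 39 and 13, and the ratio is still three.
- OUT and ART: 3 sessions by months 17-18; only 1 falls in months 1-6.

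| Component | 6 months | 18 months |
|---|---|---|
| Toothpaste rounds | 3 | 9 |
| Toothbrushes (every 3 months) | 2 | 6 |
| OUT/ART sessions | 1 | 3 |
| Education sessions | about 12 | 36 |

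Every row differs by a factor of three. No component in 4.6 or Table 1 stops at month 6, so six months cannot refer to one part of the package.

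**2. Time since the end of the intervention** = visit month minus duration.

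| Visit | Package ends at month 6 | Package ends at month 18 |
|---|---|---|
| Month 18 | 18 - 6 = 12 months after | 18 - 18 = 0 |
| Month 24 | 24 - 6 = 18 months after | 24 - 18 = 6 months after |

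**3. Objective 4 as written in Appendix 6** (visits at 6 and 12 months). With a six-month package the lags are 6 - 6 = 0 and 12 - 6 = 6 months after the end. With an 18-month package both visits fall during delivery, 12 and 6 months before it ends.

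**4. Mitigation 3.** A stop six months before the last visit is month 24 - 6 = 18. A six-month package would stop 18 months before that visit.

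**5. Budget check (section 5.0).** 570 dozen toothpastes is 6,840 packs and 380 dozen toothbrushes is 4,560.
- At the 18-month rate: 6,840 / 9 = 760 and 4,560 / 6 = 760 participants.
- At the six-month rate: 6,840 / 3 = 2,280 and 4,560 / 2 = 2,280, more than the whole sample of 1,760.
- At a 24-month rate: 6,840 / 12 = 570 and 4,560 / 8 = 570.

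The quantities do not fit six months and cannot separate 18 from 24.

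**6. Sample size.** The 1,760 in section 4.4 uses no intervention duration, so this point does not affect it.

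**The case against.** The best defence is that every passage specifying delivery agrees. Section 4.6 gives 18 months for toothpaste, toothbrushes and education, Table 1 gives it for all four components, and 4.14 depends on it. Field staff have one coherent schedule. The randomised comparison, the visits and the generalized estimating equations do not change with the label. This stands, and it limits the harm to what the objectives say is being estimated. It does not remove the contradiction, because the six-month wording occurs seven times, including in the table that ties objectives to analyses.

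A reader might infer more in two respects.

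- **A third, 24-month intervention in 4.6.2.** On that reading delivery would still be running at month 18 and ending at month 24. The heading and grammar allow it, but the phrase ends in follow-up, it matches the last visit, and Table 1 rules out all four components in months 19-24. It may mean only total follow-up. The passage is ambiguous and does not establish a third duration.
- **Policy makers will be given the wrong exposure.** This assumes that the authors will report the label in the objectives and not the schedule delivered. Nothing in the protocol shows that they would.

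**Conclusion.** The contradiction is firm and two-way: six months in 1.3, 2.2 and Appendix 6, against an end at month 18 in 4.6, Table 1 and 4.14. Its size is a threefold difference in exposure, and lags at the 18- and 24-month visits of 12 and 18 months or of 0 and 6 months. Followed literally, the objectives ask about durability, while the schedule yields an end-of-intervention result and a six-month post-intervention result.

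A separate conflict concerns caries, part of a primary outcome: it is assessed at 18 and 24 months in 2.2 but at 6 and 12 in Appendix 6. Only the rows for objectives 3 and 5 in Appendix 6 agree with 2.2 on visits.

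The conclusion rests on the stated durations, intervals and visit months, with education counted at two sessions per month as Table 1's total implies. It does not rest on reading 4.6.2 as a 24-month intervention.

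**What to change.** Reconcile 1.3, 2.2, 4.6, 4.6.2, Table 1, 4.14 and Appendix 6 to one intervention period. Which period is for the investigators to settle; this review does not propose one. Then:

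- Reword objectives 3-5 and their Appendix 6 rows to that period.
- Make the assessment times for objective 4 the same in 2.2 and Appendix 6.
- In 4.6.2, give the intervention period and the total follow-up as separate figures.
- For each assessed visit, state the time since the intervention ended, or that it is still running, so that the conclusions describe the intervention actually delivered.
- Check that Mitigation 3 still holds under the agreed period.

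The cost is a wording amendment. If the settled period is the one already scheduled, neither the sample size nor the visits change.
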